### Economic evaluation

A cost-consequences economic evaluation, will evaluate the effectiveness of the community-based intervention compared to current practice. Information collected during the process evaluation will be used to calculate the cost of the intervention for each ward including development and implementation costs. Health care resource use, collected for both trial arms, will include: antenatal bookings and appointments; antenatal admissions; mode of delivery with a focus on emergency cesareans; costs associated with pre-term births and low birth weight, maternal and infant deaths.

## Analysis

### Trial outcomes

A cluster-level analysis, appropriate to the analysis of matched cluster randomised trials, will be used with the maternity care providers for the NHS trusts participating in the study as fixed effects. We will use intention to treat principles. We will include individual level prognostic covariates if appropriate and ward-level estimates of baseline levels of outcomes as covariates. These will be chosen in advance of any analyses being conducted and documented in a full analysis plan. In additional analyses we will explore the use of instrumental variable techniques to incorporate some process measures as mediators of effect. Our primary analyses will consider primary and secondary outcomes data pertaining to births in the period 2–7 months post intervention start. Further secondary analyses will be conducted using data for births in the period 8–13 months post intervention completion to explore the maintenance of any effects and trends. A small number of sub group analyses may also be conducted using Stata software (version 14; StataCorp, College Station, TX, USA).

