**Methods/design:**

The study design is a matched cluster randomised controlled trial with integrated process and economic evaluations. The unit of randomisation is electoral ward. The intervention will be delivered in 10 wards; 10 comparator wards will have normal practice. The primary outcome is the proportion of pregnant women attending their antenatal booking appointment by the 12th completed week of pregnancy. This and a number of secondary outcomes will be assessed for cohorts of women (*n* = approximately 1450 per arm) who give birth 2–7 and 8–13 months after intervention delivery completion in the included wards, using routinely collected maternity data. Eight hospitals commissioned to provide maternity services in six NHS trusts in north and east London and Essex have been recruited to the study. These trusts will provide anonymised routine data for randomisation and outcomes analysis. The process evaluation will examine intervention implementation, acceptability, reach and possible causal pathways. The economic evaluation will use a cost-consequences analysis and decision model to evaluate the intervention. Targeted community engagement in the research process was a priority.

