### Study population

The study population is women in the selected electoral wards who give birth, at a hospital enrolled in the study, over a 12-month period. The timing of this period will be determined by the delivery of the intervention; all women in control and intervention sites will be included if they give birth 2–13 months after the intervention delivery has ended in intervention sites. There will be no active recruitment of participants to this trial as outcomes will be measured using anonymised routinely collected maternity services data. Individuals will be recruited to the integral process evaluation and this is described below.

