### Outcome measures

Based on the hypothesis that the intervention will promote earlier booking of care, particularly by those most at risk of late booking (as per the pathways shown in Fig. 1), the primary outcome is the proportion of pregnant women in each ward who have attended their antenatal booking appointment by the end of the 12th completed week of their pregnancy. Secondary outcome measures are: the proportion of women who have attended their antenatal booking appointment by 10 weeks and 0 days of pregnancy; antenatal admissions; emergency caesarean rates; gestation and weight at delivery; smoking at booking appointment and at birth; feeding method at discharge. Outcomes will be measured using anonymised routine hospital data. Outcomes data, covering periods of 6 months, will be extracted by trust informatics staff at three time points. These time points are as follows: time point 1 (baseline) – women giving birth who were at least 13 weeks pregnant at the point that any intervention-related activities commenced; time point 2 (first follow-up) – women giving birth 2–7 months after the end of intervention delivery; time point 3 (second follow-up) – women giving birth 8–13 months after the end of intervention delivery. Further data on age, ethnicity, housing tenure, parity and deprivation will be provided along with the outcomes data.

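### The sentence defining the primary analysis counts births from intervention start; the rest of the protocol counts them from the end of delivery, six months later

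*Protocol article*

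**What the plan says.** Protocol article, Analysis, Trial outcomes: "Our primary analyses will consider primary and secondary outcomes data pertaining to births in the period 2–7 months post intervention start". The next sentence of that paragraph assigns the further secondary analyses to "births in the period 8–13 months post intervention completion". Two adjacent sentences therefore use two different anchors.

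The other statements of the window all use the end of delivery:

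- Abstract, Methods/design: cohorts of women "who give birth 2–7 and 8–13 months after intervention delivery completion".
- Study population: women in both arms are included if they "give birth 2–13 months after the intervention delivery has ended in intervention sites".
- Outcome measures, time point 2 (first follow-up): "women giving birth 2–7 months after the end of intervention delivery". Time point 3 covers months 8–13 from the same anchor.

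Safety and trial conduct adds that outcomes data are first collected once delivery is complete. That fits the end anchor, although on its own it fixes when data are extracted and not which births are included.

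**The concern.** The primary outcome is settled early in pregnancy: a woman either has or has not attended booking by the end of the 12th completed week. For a birth at term, that moment lies roughly six months before delivery. Moving the birth window by 6 months therefore moves the decision point from during the intervention to mostly before it.

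The Trial outcomes sentence is the only one that says which births form the primary analysis. Study population and Outcome measures define who is eligible and when data are extracted, but neither says which period is primary. A wrong anchor in this sentence could be copied into the analysis plan or into the instructions to trust informatics staff. Until it is corrected, the published protocol states the primary cohort in two incompatible ways.

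**Working it through.** **Reproducing the plan's own figures (Power and sample size).** For 75% versus 82%, two-sided 5% and 90% power, the usual two-proportion formula gives 722 per arm, and 751 with continuity correction, as stated. The design effect is 1 + (145 − 1) × 0.005 = 1.72. Then 751 × 1.72 = 1292, and 1292 / 145 = 8.9, so 9 clusters, also as stated.

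**Inputs for the timing check.**

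- From the protocol: implementation 6 months and set-up 3 months (The intervention); cut-off at the end of the 12th completed week, taken as 13w0d; extractions covering 6 months (Outcome measures).
- Assumed, not in the protocol: birth at 40 weeks (range 37–41), births spread evenly over the window, and 4.348 weeks per month.
- The range 2–7 months is read as 2.0–7.0, as 2.0–8.0 (six months inclusive), or as 1.0–7.0. Months are counted per site.

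**Where the windows fall, in months from the start of implementation.**

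| Window | Months from start |
|---|---|
| Primary, as written (start + 2–7) | 2–7 |
| Time point 2 (end + 2–7) | 8–13 |
| Secondary, as written (completion + 8–13) | 14–19 |

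Time point 2 is covered by neither analysis as written. In months from the end of delivery, the literal primary window runs from −4 to +1 (to +2 on the inclusive reading). The study population begins at +2.

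**Share past the cut-off when implementation starts.** With birth at 40 weeks, 13w0d falls 27 / 4.348 = 6.21 months before birth. A woman giving birth t months after the start therefore reaches it at t − 6.21 months: −4.21 for t = 2, +0.79 for t = 7, and +1.79 for t = 8.

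- Window 2.0–7.0: (6.21 − 2) / 5 = 84%
- Window 2.0–8.0: (6.21 − 2) / 6 = 70%
- Window 1.0–7.0: (6.21 − 1) / 6 = 87%

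Varying birth from 37 to 41 weeks and the cut-off between 12w0d and 13w0d gives 59% (37 weeks, 13w0d, window 2.0–8.0) to 94% (41 weeks, 12w0d, window 1.0–7.0). If start means the beginning of the 3-month set-up, every woman is past the cut-off when implementation begins.

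**Same check with the end anchor.** No woman is past the cut-off at the start of implementation on any of these readings. With birth at 40 weeks and the window 2.0–7.0, 13w0d is reached between 8 − 6.21 = 1.79 and 13 − 6.21 = 6.79 months after the start. At 41 weeks the earlier limit is 8 − 28 / 4.348 = 1.56 months.

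**Illustration of dilution.** Suppose the full 7-point gain applies only to women who reach 13w0d after the start, and that nobody else changes. The diluted effect is 7 × 0.16 = 1.1 points (window 2.0–7.0) or 7 × 0.30 = 2.1 points (window 2.0–8.0). For a paired t-test with k = 10 pairs, m = 145, ICC ρ = 0.005 and matching correlation r = 0.1, the variance of a pair difference is the sum over arms of p(1 − p)[(1 − ρ)/m + ρ(1 − r)], with 9 degrees of freedom.

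| True difference | SE | Effect / SE | Power |
|---|---|---|---|
| 7 points | 0.0195 | 3.59 | 89% |
| 2.1 points | 0.0203 | 1.03 | 15% |
| 1.1 points | 0.0205 | 0.54 | 8% |

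A normal approximation with 1450 per arm and design effect 1.72 gives about 94%, falling to 6–17% over diluted effects of 0.9 to 2.1 points. The conclusion is the same.

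**The case against.** The best defence is that the rest of the protocol already settles the cohort. Study population admits only births from 2 months after delivery has ended. Outcome measures lists three extractions, and neither follow-up extraction supplies births from −4 to +1 or +2 months around the end of delivery. Only the baseline extraction could overlap them. The following sentence treats months 8–13 as a test of whether effects are maintained, which makes sense only if months 2–7 share its anchor. An analyst using the planned follow-up data could not apply the start anchor literally. All of this stands, and it is why the sentence is best read as a slip.

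A reader might go further and infer any of three things that the document does not support:

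- **The trial will analyse an unexposed cohort.** The population and extraction rules stand in the way, and the statistical analysis plan, which is not shown, may already have the right anchor.
- **The investigators could choose between two cohorts after seeing the data.** The follow-up extractions contain only one of them.
- **A null result is guaranteed.** Even on the literal window, 6–41% of women would still be before the cut-off when implementation began. The argument also concerns the booking outcomes: antenatal admissions, smoking at birth and feeding at discharge are not fixed at 13 weeks.

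The power figures also rest on assumptions that the protocol does not make, including the paired t-test; it specifies only a cluster-level analysis suited to matched designs.

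**Conclusion.** The contradiction is real and should be corrected. As written, the sentence that fixes the primary analysis names a cohort 6 months earlier than the one described in the abstract, Study population and Outcome measures. That most of the literal cohort would be past the booking cut-off before implementation holds on every reading tried (59–94%; about 70–84% for 40-week births). It depends on births at 37–41 weeks, an even spread of births and months counted per site. By calendar arithmetic alone, the time point 2 births would be left out of both analyses.

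The loss of power from about 89% to about 8–15% shows what literal use would cost for the booking outcome. It is not a forecast for this trial. The correction matters because of where the sentence stands; the weight of the text makes a failed primary analysis unlikely.

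**What to change.** In Analysis, Trial outcomes, replace the start anchor so that the primary analyses cover the births already defined as time point 2, "women giving birth 2–7 months after the end of intervention delivery". This agrees with the abstract, Study population and Outcome measures. Then confirm that the statistical analysis plan and the data-extraction specification sent to the trusts use the same anchor. The cost is one corrected phrase and a check of two documents. No new data, design change or sample-size revision is needed.

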### Process evaluation

All qualitative interview data will be managed and coded using QSR International’s NVivo 11 qualitative data analysis software. Interview data will be subjected to thematic analysis. Codes will be applied to transcripts, to identify key themes and how these inter-relate in order to develop an analytical framework. Each transcript will also be coded to indicate the type of participant and electoral ward allowing analytical themes to be explored in relation to different groups’ experiences and to compare processes across intervention areas. Drawing on methods associated with ‘grounded theory’, constant comparisons will be made and deviant cases examined to refine the analysis.

Observation data will be recorded on a semi-structured proforma. Thematic analysis of this data will also be undertaken.

Data from the surveys will be analysed using the current version of IBM SPSS statistical software. Descriptive analysis will be conducted to assess the key themes relating to awareness and level of involvement with the intervention, attitudes towards it, and views on antenatal care.

### Economic evaluation

Costs and health care resource will be reported alongside primary and secondary outcomes for each trial arm. Missing data will be assumed to be missing at random and available case analysis used following the principles set out in the statistical analysis plan. We will report 95% confidence intervals calculated using bootstrapping.

A decision analytic model will also be developed to extrapolate the outcomes collected, antenatal admissions and emergency caesarean, their impact on costs and health outcomes and costs published in the literature for pre-term and low weight births. We will use a simplified decision analytical model to look at the benefits and disadvantages of the intervention, including the impact on the 12th completed week of pregnancy target, to assist NHS trusts with decisions about implementation; synthesising information from other sources where at all possible.

## Safety and trial conduct

There are no anticipated risks to study participants or to those involved with the intervention and the first outcomes data collection will occur after the intervention delivery is complete. Therefore, there will be no Data Monitoring Committee for this trial. This decision, made by the chief investigator (AH) and members of the Trial Steering Committee (TSC; see below), is due to the reliance on routine monitoring data that is provided at source in non-identifiable form. However, as in all interventions, there may be unanticipated risks and harms will be assessed through examination of outcomes at the two time points.

The UK MRC Guidelines on good clinical practice in trials [27] will be followed. The University of East London, the employer of AH, will act as the sponsor of this trial. The trial will be overseen by a TSC. This group will meet face to face once a year and will be responsible for overseeing the trial, ensuring scientific quality and clinical relevance, and adherence to ethics and research governance. All key collaborators on the trial will attend the TSC, as well as a range of experts who are not directly involved in the trial, including a chair with relevant expertise, a statistician and an economist. There will also be a maternity service user representative on the TSC. Bi-monthly trial management meetings, with the PCTU, will be held and study team meetings, involving AH, MW, MS, LS and CS, will take place once a month to oversee day-to-day progress.

## Dissemination

The findings of the trial will be presented at national and international conferences (e.g. Royal Colleges of Midwives annual conference, the International Confederation of Midwives Congress and relevant national public health conferences). They will also be published in peer-reviewed academic journals and in professional and practitioner journals. Findings will also be made available on the study website and in newsletters. Briefing papers to health care commissioners and managers and to service users via Maternity Voices Partnerships, will be prepared. We will use links with the Reproductive and Childbirth topic network to further disseminate throughout the NHS.

## Discussion

The Community REACH trial is one of a growing number of randomised controlled trials of public health interventions. The antenatal intervention being tested in the trial builds on evidence of effectiveness of lay or peer-delivered interventions when using community engagement strategies to provide health interventions to vulnerable or disadvantaged populations. A number of elements of the study will aid generalisability and scalability if effectiveness is shown. These elements include the integrated process and economic evaluations, the range of participating providers of maternity care in the trial, the flexibility of the intervention and the central involvement of local community members and community organisations. The application of a cluster randomised controlled trial design to the testing of an intervention that combines standardisation of overall approach with adaption to the local context will make a valuable contribution to the existing body of work on study design, as will the use of routine hospital data for outcomes analysis and the collaborative approach to research processes. If the intervention is shown to be effective it will be of benefit to those who received it and to society generally, in terms of improved health and associated reduction in cost to society and the NHS.

## Trial status

The study protocol reported here is version 2 (22 January 2016). There will be no active recruitment of participants to this trial as outcomes will be measured using anonymised routinely collected maternity services data. Individuals will be recruited to the integral process evaluation; recruitment began in June 2017 and is expected to finish in June 2018.

## Abbreviations

ANC: Antenatal Care
CLAHRC: Collaboration for Leadership in Applied Health Research and Care
IT: Information Technology
MRC: Medical Research Council
NIHR: National Institute for Health Research
PCTU: Pragmatic Clinical Trials Unit
PGfAR: Programme Grants for Applied Research
PI: Principal investigators
QMUL: Queen Mary’s University London
SPIRIT: Standard Protocol Items: Recommendations for Interventional Trials
TSC: Trial Steering Committee
UCL: University College London
UEL: University of East London
